### Randomisation

All patients diagnosed with a displaced complete articular AO/OTA type C distal radius fracture will be invited to participate in this study. Patients will be approached by the investigators to participate in this study after adequate reduction of the fracture has been obtained. Patients will receive a patient information sheet with both the contact information of the coordinating investigator and the independent expert. Possible participants will have till the first outpatient appointment to decide to participate or not. This first outpatient appointment will be about 7 days after the initial trauma. If a patient decides to participate, oral and written informed consent will be obtained. Possible participants can be approached and included in this study up to the first outpatient visit.

After obtaining informed consent, patients will be randomised into either the intervention group (open reduction and plate fixation) or the control group (closed reduction and plaster immobilisation). In order to avoid any potential imbalances between the two treatment groups, patients will be randomised in two strata according to age: 18 to 40 and 41 to 65 years.

To ensure concealment of allocation, randomisation will be performed by means of a mixed block, computerised randomisation. The distribution and order of the block sizes are unknown to the researchers, who therefore remain blinded to the allocation of the next subject throughout the whole study. Surgery will be performed within two weeks after randomisation. All the participating centres can perform the randomisation on the study website (www.viparstudie.nl), where each centre has his own personal username and password. After randomisation the allocation is shown on the website.

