### Sample size calculation and data analysis

The sample size calculation is based on our primary endpoint, the PRWE score. The mean PRWE score after open reduction and volar locking plate fixation after one year of follow-up in patients aged over 18 years with a dorsally displaced distal radius fracture is 15 with a standard deviation of 17 [41]. This figure was measured in a patient population in which 33 % suffered from a displaced complete articular distal radius fracture (AO/OTA type C fracture). The same mean and standard deviation were found in a study of MacDermid et al. [42].

The minimal clinical important difference (MCID) is the minimal change in score that is considered as meaningful to patients [30]. The MCID of the PRWE score is 14 points according to Sorensen et al. [43]. Thus, to demonstrate a difference that is clinically relevant, we need to power on a difference of 14 points. Any difference smaller than this is not clinically relevant.

Therefore at α = 0.05 % and a power of 90 %, we would require 64 patients in total and 32 per treatment arm. For safety measures, to correct for deaths and with an expected lost to follow-up of 10 %, 90 patients (45 patients in each arm) will be included. From a separate study being conducted by our research group at two teaching hospitals, it was found that of the 494 distal radius fractures encountered in one year, 126 (25 %) were an AO/OTA type C [2]. Therefore we estimate to require a maximum of 2 years to include and follow-up the patients in this trial.

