All patients will be analysed according to the results of the randomisation (intention-to-treat). Patient characteristics at baseline, such as gender and age, will be described by general descriptive statistics. Differences in the primary outcome (PRWE at one year) between the two groups will be analysed using the Unpaired *T*-test (if normally distributed) or the Mann–Whitney *U* test (if not normally distributed). Trends in PRWE-scores among the different time points will be assessed using multiple linear regression. The secondary outcomes; DASH-scores, quality of life (SF-36), pain (as indicated on a Visual Analogue Scale (VAS)), range of motion (ROM) and grip strength will be analysed in a similar manner. Differences between the two treatment groups in radiological outcomes, crossovers and complication rates will be analysed using the Chi-square test or the Fischer’s Exact test (in case the expected incidence was less than five). Subgroup analyses will be performed on gender and age (18 to 40 years and 41 to 65 years) for all outcomes.

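### Randomisation is stratified by age but the primary test leaves the stratum out; if age is related to PRWE, the interval is slightly too wide and the test conservative

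*Protocol article*

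**What the plan says.** Under Randomisation, the protocol article says "patients will be randomised in two strata according to age: 18 to 40 and 41 to 65 years". The reason given is "In order to avoid any potential imbalances between the two treatment groups". Allocation is blocked: "randomisation will be performed by means of a mixed block, computerised randomisation".

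Under Sample size calculation and data analysis, the primary comparison is named: "Differences in the primary outcome (PRWE at one year) between the two groups will be analysed using the Unpaired" t-test, with the Mann-Whitney U test as the alternative if the data are not normal. Neither test carries the age stratum or any other covariate. The continuous secondary outcomes follow the same approach, and crossovers and complications get an unstratified chi-square or Fisher test. Multiple linear regression is named for PRWE over time, not for the one-year comparison. Age comes back only here: "Subgroup analyses will be performed on gender and age (18 to 40 years and 41 to 65 years) for all outcomes".

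**The concern.** Blocking within age strata forces the arms to be nearly balanced on age. Any part of the PRWE variance that comes from the stratum then contributes almost nothing to the true sampling variance of the treatment difference. An unpaired t-test does not know this: its standard error is built from the total within-arm variance, which still contains the between-stratum part. If age is related to PRWE, the reported interval is wider and the p-value larger than the design warrants.

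What is at stake is precision. The trial takes the trouble to balance on age and then does not collect the benefit in the analysis. The article names its primary test explicitly, so this is a mismatch between two things it states, not a detail left to an analysis plan.

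**Working it through.** **Inputs from the protocol article (Sample size calculation and data analysis).** The one-year PRWE "is 15 with a standard deviation of 17"; "we need to power on a difference of 14 points"; power 90%; 32 evaluable per arm (64 in total); 90 recruited with 10% loss expected. Alpha is printed in "at α = 0.05 % and a power of 90" %.

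**Step 1: reproduce the planned size.** The normal approximation is n per arm = 2(1.960 + 1.282)² × 17² / 14² = 31.0, so 31. The t-test version gives 31.98, so 32 per arm and 64 in total, with power 0.900. This matches the article if alpha is 0.05 two-sided. The printed 0.05% (0.0005) would need 134 in total. The planned size therefore rests on an unadjusted two-group comparison with total SD 17.

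**Step 2: what a stratum effect does.** Let R² be the share of PRWE variance explained by the age stratum. The documents do not give it; 2-10% is an assumption.

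- Excess standard error = 1/√(1 − R²) − 1.
- True size of the nominal 5% test = 2[1 − Φ(1.96/√(1 − R²))].
- Difference between equal-sized strata that gives this R² at SD 17: d = √(R² × 289 / 0.25).

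| Assumed R² | d (points) | Excess SE | True size |
|---|---|---|---|
| 0.02 | 4.8 | 1.0% | 4.8% |
| 0.05 | 7.6 | 2.6% | 4.4% |
| 0.10 | 10.8 | 5.4% | 3.9% |

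In patients, the loss is about R² × 90, which is 2 to 9 of the 90 recruited.

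**Step 3: check by simulation.** Randomisation was simulated in blocks within two equal-sized age strata (block sizes 2, 4 and 6 assumed), with 32 per arm, total SD 17 and normal errors. There were 4000 runs under no treatment effect and 2000 at 14 points. The unadjusted t-test was compared with a linear model on treatment and stratum.

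| Assumed age difference (points) | CI width, adjusted/unadjusted | Type I error, unadjusted | Coverage, unadjusted | Power, unadjusted → adjusted |
|---|---|---|---|---|
| 0 | 1.000 | 0.054 | 0.946 | 0.910 → 0.910 |
| 3 | 0.997 | 0.053 | 0.947 | 0.892 → 0.896 |
| 5 | 0.989 | 0.046 | 0.954 | 0.894 → 0.900 |
| 10 | 0.956 | 0.039 | 0.961 | 0.904 → 0.925 |
| 14 | 0.911 | 0.036 | 0.964 | 0.914 → 0.938 |

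The simulation standard error is about √(0.05 × 0.95/4000) = 0.003 for type I error, so 0.053-0.054 in the first two rows is compatible with 0.05. The width ratios at 5 and 10 points equal √(1 − R²) for R² = 0.022 and 0.087, so formula and simulation agree. With 75% of patients in the older stratum the ratios are closer to 1: 1.001, 0.998, 0.993, 0.967 and 0.935.

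**Limit of the check.** These figures are for the t-test. The mean of 15 is less than one SD (17) above the floor of a 0-100 scale, so the Mann-Whitney branch may well be the one used. The reasoning about balanced strata carries over to it, but no figure was computed for it.

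**The case against.** The strongest objection is that nothing important is lost. The excess width depends on an age effect that the documents do not give. The top of the assumed range needs a gap of nearly 11 points between age groups, about three quarters of the 14-point MCID (10.8/14 = 0.77), or 12.4 points with a 75/25 split. The error is on the safe side. The sample also has slack: 90 less 10% leaves 81, which is 17 more than the 64 needed, and normal-approximation power at 40 per arm is already 0.958. All of this stands, and it is why the point is minor.

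A reader might infer that the protocol stratified because it expects age to affect PRWE. The article does not say so; its only stated reason is avoiding imbalance. Nor does the plan neglect age altogether, since it has subgroup analyses in exactly these strata. Those do not, however, correct the standard error of the primary comparison.

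A fuller analysis plan, not shown, could add the stratum. It would then depart from the primary test that the article names, so the article's text is still worth correcting.

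**Conclusion.** The point holds as a conditional and minor one. The stated primary test omits the factor used to stratify. If the stratum explains an assumed 2-10% of PRWE variance, the unadjusted standard error is about 1-5% too large and the true size is 4.8-3.9%. In the simulation with equal strata, the power gained by adjusting is under 1 percentage point for age differences up to 5 points and about 2 points at 10-14. With no age effect the two analyses practically coincide.

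Two stronger readings are tempting and not supported. The first is that the intervals will be too wide as a matter of fact: that requires an association between age and PRWE, for which the documents give no figure. The second is that the primary analysis is invalid: the unadjusted difference is unbiased, type I error is not inflated, and coverage is at or above nominal within simulation error. Nothing here threatens the trial's conclusion or its sample size.

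**What to change.** Make the primary analysis a linear model of one-year PRWE on treatment and age stratum (18-40 / 41-65), and report the adjusted mean difference with its 95% CI, which can be read against the 14-point MCID. Where the plan would turn to Mann-Whitney, use a rank test stratified by age (van Elteren). Keep the unadjusted test as a sensitivity analysis.

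Treat the continuous secondary outcomes in the same way. For binary outcomes, use a Mantel-Haenszel analysis stratified by age where counts allow, and keep Fisher's exact test where they are sparse; a logistic model is not needed and could be unstable there.

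The cost is a few sentences in the analysis section and one degree of freedom in the model. The stratum is known for every randomised patient, no new data are needed, and the 64 evaluable patients remain sufficient. If age turns out to have no effect, the simulated interval width is practically unchanged (ratio 1.000-1.001).

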### Blinding

Randomisation status will not be blinded since the assigned treatment involves a surgical procedure.

### Sample size calculation and data analysis

The sample size calculation is based on our primary endpoint, the PRWE score. The mean PRWE score after open reduction and volar locking plate fixation after one year of follow-up in patients aged over 18 years with a dorsally displaced distal radius fracture is 15 with a standard deviation of 17 [41]. This figure was measured in a patient population in which 33 % suffered from a displaced complete articular distal radius fracture (AO/OTA type C fracture). The same mean and standard deviation were found in a study of MacDermid et al. [42].

The minimal clinical important difference (MCID) is the minimal change in score that is considered as meaningful to patients [30]. The MCID of the PRWE score is 14 points according to Sorensen et al. [43]. Thus, to demonstrate a difference that is clinically relevant, we need to power on a difference of 14 points. Any difference smaller than this is not clinically relevant.

Therefore at α = 0.05 % and a power of 90 %, we would require 64 patients in total and 32 per treatment arm. For safety measures, to correct for deaths and with an expected lost to follow-up of 10 %, 90 patients (45 patients in each arm) will be included. From a separate study being conducted by our research group at two teaching hospitals, it was found that of the 494 distal radius fractures encountered in one year, 126 (25 %) were an AO/OTA type C [2]. Therefore we estimate to require a maximum of 2 years to include and follow-up the patients in this trial.

All patients will be analysed according to the results of the randomisation (intention-to-treat). Patient characteristics at baseline, such as gender and age, will be described by general descriptive statistics. Differences in the primary outcome (PRWE at one year) between the two groups will be analysed using the Unpaired *T*-test (if normally distributed) or the Mann–Whitney *U* test (if not normally distributed). Trends in PRWE-scores among the different time points will be assessed using multiple linear regression. The secondary outcomes; DASH-scores, quality of life (SF-36), pain (as indicated on a Visual Analogue Scale (VAS)), range of motion (ROM) and grip strength will be analysed in a similar manner. Differences between the two treatment groups in radiological outcomes, crossovers and complication rates will be analysed using the Chi-square test or the Fischer’s Exact test (in case the expected incidence was less than five). Subgroup analyses will be performed on gender and age (18 to 40 years and 41 to 65 years) for all outcomes.

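### The protocol prints its only significance level as 0.05 % (0.0005), but its 32 patients per arm follow from a two-sided 0.05 (5 %): the sample size is right and the printed alpha is wrong

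*Protocol article*

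**What the plan says.** All of the relevant text is in the protocol article, section Sample size calculation and data analysis.

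- The outcome is the PRWE at one year. After plate fixation its mean "is 15 with a standard deviation of 17".
- The target difference is the minimal clinically important difference: "we need to power on a difference of 14 points".
- Significance level, power and result: "Therefore at α = 0.05 % and a power of 90 %, we would require 64 patients in total and 32 per treatment arm".
- Inflation: "For safety measures, to correct for deaths and with an expected lost to follow-up of 10" per cent, the total is raised, so that "90 patients (45 patients in each arm) will be included".
- The primary comparison "will be analysed using the Unpaired *T*-test (if normally distributed) or the Mann–Whitney *U* test (if not normally distributed"). No alpha and no sidedness are given there.

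**The concern.** An alpha of 0.05 % is 0.0005, a hundred times stricter than 0.05. No other place in the article gives a significance level, so nothing elsewhere corrects it. A reader who checks the calculation as printed cannot arrive at 32 per arm, and a reader who takes the sentence at its word would believe that the primary comparison is to be judged against 0.0005. The significance level is a basic design parameter, and the document states a wrong value for it rather than leaving it to another document.

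A smaller matter is the step from 64 to 90. Only one of the three allowances named has a figure, so 90 cannot be derived from what is printed.

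**Working it through.** **Inputs.** Difference δ = 14, SD σ = 17, power 90 %, 1:1 allocation and the unpaired t-test, all from the section named above. Two assumptions are needed. The SD is given for plate fixation only and is taken as common to both arms. Sidedness is not stated, so both were tried.

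**Formulas.** The standardised difference is 14/17 = 0.824. The normal approximation per arm is

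n = 2σ²(z_α + z_β)²/δ² = 2 × 289/196 × (z_α + 1.282)² = 2.949 × (z_α + 1.282)²,

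where z_α is the critical value for the chosen alpha and sidedness. The exact figure is the smallest n for which the t-test has at least 90 % power under the noncentral t distribution.

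**Reproducing the plan's figure.** At two-sided alpha 0.05, z_α = 1.960:

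- Normal approximation: 2.949 × 3.242² = 31.0, so 31 per arm.
- Exact t-test: 32 per arm, power 90.02 %. This matches 32 per arm and 64 in total.

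**The printed alpha.** At two-sided alpha 0.0005, z_α = 3.481:

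- Normal approximation: 2.949 × 4.763² = 66.9, so 67 per arm.
- Exact t-test: 70 per arm.

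| Alpha | Sides | n per arm, exact t-test | n per arm, normal approximation |
|---|---|---|---|
| 0.0005 (as printed) | two | 70 | 67 |
| 0.0005 (as printed) | one | 65 | 62 |
| 0.05 | two | **32** | 31 |
| 0.05 | one | 26 | 26 |

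Planning for the Mann–Whitney test does not rescue the printed value. Dividing by an assumed relative efficiency of 0.955 gives 70/0.955 = 73.3, so 74 per arm at two-sided 0.0005.

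**From 64 to 90.**

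- 10 % loss alone: 64/(1 − 0.10) = 71.1, so 72 in total (36 per arm).
- Margin beyond that: 90 − 72 = 18 patients.
- Total allowance implied by 90: 1 − 64/90 = 28.9 %.
- If loss is exactly 10 %, 90 × 0.9 = 81 patients remain. With 40 per arm the two-sided t-test at 0.05 has about 95 % power for 14 points.

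**The case against.** The best defence is that this is a stray percent sign and the calculation behind it is sound. That stands. Of the readings tried, only two-sided 0.05 with a t-test gives exactly 32, so the intended level can be recovered from the paragraph's own numbers. It does not make the printed value right: the sign is used properly for the power and for the loss to follow-up in the same paragraph, and no other passage gives an alpha to set against it.

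Three stronger readings might be inferred, and the document supports none of them.

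- *The trial is too small and needs 70 per arm.* At alpha 0.0005, 32 per arm would have about 36 % power and 45 per arm about 61 %. Those figures describe a trial that nobody planned, since the stated 32 itself identifies 5 % as the design level.
- *The primary outcome will be tested at 0.0005.* The slip is in the sample size sentence. The analysis text sets no threshold, and a statistical analysis plan, which is not shown, may do so.
- *A 10 % loss is claimed to turn 64 into 90.* The sentence gives three reasons for 90: safety, deaths and the 10 % loss. It never attributes the whole increase to the last. Likewise, the 90 % power is attached to 64 patients, so higher power with 90 is the expected effect of a margin and no contradiction.

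It is also tempting to explain the 18 extra patients as cover for crossover from plaster to surgery or for uncertainty in the SD. The article says neither. Nor does it give a death rate from which the share of the margin needed for deaths could be judged. A condensed article may leave such a breakdown to the full protocol.

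**Conclusion.** The stated significance level is wrong by a factor of 100 and should be corrected, because it is the only one in the document. The sample size of 32 per arm is right for a two-sided alpha of 0.05, a 14-point difference, a common SD of 17, 90 % power and an unpaired t-test. The conclusion rests on the common SD and on two-sidedness, which the article does not state; one-sided 0.05 would give 26. The mismatch at the printed alpha does not depend on method or sidedness, since every version tried gives 62 or more per arm.

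The route from 64 to 90 is a minor reporting matter. The margin of 18 beyond the 10 % loss has no figure behind it, but it errs towards more power and does not conflict with the text.

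**What to change.** In the sample size paragraph, replace the printed alpha with a two-sided α of 0.05 (5 %). This is a correction of one line. Recruitment, the sample size and the analysis stay as they are.

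Optionally, add a sentence saying that 10 % loss alone would require 72 patients and what the further 18 cover, with figures for deaths and for safety from the authors' own planning. The reason should be theirs; one should not be supplied for them.

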Since this analysis is from a societal perspective, direct health care costs, direct non- healthcare costs and indirect costs due to a distal radius fracture will be considered. Direct health care costs include treatment, follow up visits to medical specialist, any additional visits to general practitioner or other health care professionals, prescribed medication, professional home care and treatment of possible complications (Table 1). Direct non-healthcare costs include travel expenses to and from the hospital, over-the-counter medication, care provided by family or paid help and assistive devices. Indirect costs originating from loss of production or hours of inactivity due to immobilisation, pain or decreased function of the wrist will be included as well. These will be estimated using the Friction-Cost method that limits productivity loss to the friction period. This friction period is the period to recruit and train a replacement for the sick employee [36–38]. The Human Capital Approach, which is based on the total expected loss of production for an individual worker [38], will also be used to estimate costs. Compared with the Friction-Cost method, the Human Capital Approach will often overestimate costs from a societal perspective, especially in the long term [37, 39].

**Table 1 Tab1:** Costs included in the economic evaluation

Direct health care costs	
Closed Reduction and Plaster immobilisation	
Open reduction and internal fixation	
Follow-up visits medical specialist	
Additional visits to health care professional	
Prescribed medication	
Professional home care	
Treatment and follow up of complications	
Physical therapy	
Direct non-health care costs	
Travel expenses to and from the hospital	
Over the counter medication	
Care provided by family or paid help	
Assistive devices	
Indirect costs	
Absenteeism from paid labour (per day)	
Absenteeism from unpaid labour	

Data regarding the use of health care resources will be assessed using four economic evaluation questionnaires (cost diaries) which patients will be asked to fill out during the trial at six weeks and three, six and twelve months [40]. The costs of direct health care related costs will be estimated by means of Dutch guidelines (DOT system).

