## Discussion

Since the treatment allocation involves a surgical procedure, randomisation status will not be blinded. Our research group discussed the idea to let the researcher, who is assessing the outcomes at one year, be unaware of the treatment allocation. However this is practically not possible since all follow-up visits are realised by one or two researchers. At final follow-up, these researchers will have assessed the participants multiple times in the past year and will therefore be aware of their treatment allocation. Although this arrangement makes blinding impossible, the continuity of the observer is one of the strengths of this study and this will minimise intra-observer variation in the outcome measurements.

Additionally, for the measurement of the radiographic parameters we used the PACS of the participating hospitals. Although PACS is good to measure angles (inclination and dorsal or volar angulation) and the inter- and intra-observer reliability are substantial and moderate respectively [44], the linear measurement (radial length and gap or step-off) in PACS is less exact.

Last, due to the fact that patients will be analysed according to the intention-to-treat principle, possible crossovers will be analysed in the group they were allocated to.

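### Multiple linear regression, as named for PRWE trends over repeated visits, ignores within-patient correlation and gives wrong standard errors in these secondary analyses

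*Protocol article*

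**What the plan says.** All statements on analysis are in the protocol article, section Sample size calculation and data analysis.

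- **Primary comparison.** "Differences in the primary outcome (PRWE at one year) between the two groups will be analysed using the Unpaired" t-test, or the Mann–Whitney U test if the scores are not normally distributed. This uses one score per patient.
- **Course over time.** "Trends in PRWE-scores among the different time points will be assessed using multiple linear regression".
- **Continuous secondary outcomes.** DASH, SF-36, VAS pain, "range of motion (ROM) and grip strength will be analysed in a similar manner".

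The Discussion confirms that the same people are measured repeatedly: by final follow-up "these researchers will have assessed the participants multiple times in the past year". The visit schedule is in Fig. 1, which is not available in the text. The nearest stated schedule is that of the cost diaries in the Outcomes section, "at six weeks and three, six and twelve months".

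The article mentions no mixed model, generalised estimating equations (GEE), repeated-measures analysis of variance, patient random effect, clustered standard error or per-patient summary measure.

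**The concern.** A trend among time points needs more than one score per patient. Multiple linear regression in its ordinary sense treats every row of data as independent. Two scores from one wrist are not independent, so the model misjudges how much information the data hold.

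The direction of the error depends on the question asked:

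- **Changes within patients** (time trend, or difference in trend between groups). The stable part of each patient's score cancels. Ordinary regression leaves it in the residual variance, so the standard error is too large and real differences in recovery are missed.
- **A group difference averaged over visits.** Repeated scores from one patient are counted as new patients, so the standard error is too small and false positives rise.

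The first case is what the plan's wording describes. It matters here because the Background gives more rapid recovery as one of the possible advantages of plate fixation. That is a question about the course over time, which the one-year test does not address.

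**Working it through.** **1. The plan's own figure.** The sample size rests on a one-year PRWE mean that "is 15 with a standard deviation of 17" and on the statement that "we need to power on a difference of 14 points". With SD 17, difference 14, two-sided alpha 0.05 and 90% power, the t-based calculation gives 31.98, so 32 per arm and 64 in total. (The normal approximation gives 31 per arm.) This matches the plan: "and a power of 90 %, we would require 64 patients in total and 32 per treatment arm". It is a calculation for one score per patient, so the trend method does not enter it.

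**2. Inputs for the trend analysis.**
- Number of visits m: not in the text. Assumed 4, from the cost-diary times; the range 3 to 6 is also shown.
- Correlation rho between two scores of one patient: not in the text. Assumed 0.3, 0.5 and 0.7, with the same value for every pair of visits (exchangeable).
- Analysis: ordinary least squares on all visits stacked, with complete data.

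**3. Time-trend and group-by-time terms.** The true variance is (1 − rho) times the variance that ordinary regression reports. The reported standard error is therefore too large by k = 1/√(1 − rho), and the actual type I error of a nominal 5% test is 2 × (1 − Φ(1.96 × k)). This does not depend on the number of visits.

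| rho | k | Actual type I, formula | Actual type I, simulation |
|---|---|---|---|
| 0.3 | 1.20 | 1.9% | 2.1% |
| 0.5 | 1.41 | 0.6% | 0.6% |
| 0.7 | 1.83 | 0.03% | 0.1% |

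The loss of power can be put in figures. Take a difference in trend that a correct analysis would detect with 90% power, so that its true z-value is 1.96 + 1.28 = 3.24. Ordinary regression detects it only when the true z-value exceeds 1.96 × k:
- rho 0.3: threshold 2.34, power Φ(3.24 − 2.34) = Φ(0.90), about 82%
- rho 0.5: threshold 2.77, power Φ(0.47), about 68%
- rho 0.7: threshold 3.58, power Φ(−0.34), about 37%

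**4. A treatment effect pooled over visits, if one is tested.** The true variance is 1 + (m − 1) × rho times the reported one. The reported standard error is too small by r = √(1 + (m − 1) × rho), and the actual type I error is 2 × (1 − Φ(1.96/r)). With m = 4:

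| rho | r | Actual type I, formula | Actual type I, simulation |
|---|---|---|---|
| 0.3 | √1.9 = 1.38 | 15.5% | 15.3% |
| 0.5 | √2.5 = 1.58 | 21.5% | 22.5% |
| 0.7 | √3.1 = 1.76 | 26.6% | 27.6% |

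Over 3 to 6 visits and rho 0.3 to 0.8, r runs from 1.26 to 2.24 and the formula gives a type I error of about 12% to 38%.

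**5. Check on the simulation.** It used 4,000 trials per correlation, 40 patients per arm, visits at 1.5, 3, 6 and 12 months, and SD 17. In the same data, t-tests on each patient's mean and on each patient's slope kept the type I error between 4.8% and 5.6%. The distortion therefore comes from ignoring the patient as the unit.

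**The case against.** The strongest reply is that one sentence in a condensed article is being read too literally. It does not say that visits are stacked or that residuals are treated as independent. It could be loose wording for a repeated-measures model, for regression with clustered errors, or for one regression per visit. Details of this kind often stand in a full protocol or analysis plan, and those are not shown. This stands in part: what will be computed is not certain. But the article does not leave the method open. It names one, and an analyst who follows the name gets wrong standard errors. Separate regressions per visit would avoid the correlation but would not assess a trend among visits.

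Three stronger readings are tempting and are not supported.

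- **That the plan carries a 15% to 28% false-positive rate.** That figure belongs to a treatment effect averaged over visits, which the article does not announce. For the trends it does announce, the error is conservative.
- **That all comparisons are compromised.** The wording on a similar manner follows both the one-year test and the regression sentence. Comparisons of secondary outcomes at a single visit use one score per patient and are sound in this respect. Only trend analyses are exposed.
- **That the one-year test breaks the promise to analyse all patients.** In the analysis section and the Discussion, that promise concerns analysis by allocated group, including crossovers. How missing scores are handled is a separate matter, commonly left to the analysis plan.

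**Conclusion.** The point holds for the secondary trend analyses of PRWE and for any trend analysis of DASH, SF-36, VAS pain, range of motion and grip strength. The method named does not account for repeated scores from one patient, and nothing else in the article does so. Any positive within-patient correlation distorts the standard errors; only the size depends on assumptions.

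The main consequence is lost power for the time-trend and group-by-time terms. The inflated type I error is conditional on a pooled test being added. The sizes in the working are illustrative: they rest on an assumed number of visits (for the pooled test), an assumed exchangeable correlation and a literal reading of the method.

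The conclusion on the primary endpoint and the sample size of 64 do not depend on this. The change should be made, but the trial's main result is not at risk without it.

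**What to change.** In the analysis section, replace multiple linear regression with a method that accounts for within-patient correlation. One suitable choice is a linear mixed model with treatment, visit, treatment-by-visit interaction and age stratum as fixed effects and a stated within-patient covariance. GEE or regression with patient-clustered standard errors would also cure the defect. State that the same method applies to the continuous secondary outcomes measured at several visits. If a repeated-measures model was intended all along, naming it is enough.

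The cost is one sentence and standard software. No new data, visits or patients are needed, and the primary analysis stays as it is.
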